## Methods: monitoring

### Data monitoring

At 12 months after study start (17 April 2018), an interim analysis will be performed and the recruitment rate from each centre will be evaluated. The study recruitment will end once we have reached a minimum of 45 000 patients. During the second half of 2017/early 2018, the data quality of each recruiting centre will be evaluated by extracting data from each centre’s hospital information centre.

## Expected results

Our hypothesis is that the usage of this air purifier significantly lowers the incidence of SSIs after orthopaedic surgery. Since the installation, management and purchase of this kind of machines is nowhere close to the resource intensity of other types of OR ventilation arrangements, it has the possibility of introducing a cost-effective instrument to prevent postoperative infections. Furthermore, this would perhaps benefit especially resource-scarce communities globally.

Secondarily, the large amount of data derived from this study can subsequently be used analysing the effect of other kinds of exposures on the incidence of postoperative infections.

### Ethics and dissemination

The study is being conducted in accordance with the ethical principles of the Declaration of Helsinki, and is approved by the Swedish Ethical Review Authority (2015/1139-31/4).

The interim analysis results from the study will be presented only to the researchers involved unless the study thereafter is interrupted due to significant difference in infection rate between the two groups. Publication in a medical journal will be presented after inclusion of the last patient.

Study participant information will be published on the hospital web site (see online supplemental appendix 2). Due to feasibility reasons in a study with approximately 45 000 study participants, and the very low probability of any adverse effects related to the intervention, no personal consent forms will be collected. However, individual patients can request exclusion from the data analysis.

10.1136/bmjopen-2020-047500.supp2Supplementary data

The EPOS trial is registered at ClinicalTrials.gov.

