#### Multicentre power with ultra-clean air

Hospitals with ORs with ultra-clean air may be less susceptible to the effect with an already lower infection rate. Pre-study CFU measurements suggest that approximately 80% of the included ORs are ultra clean. If we assume that the infection rate is 2% or less, and that the effect size is reduced to 25% in an ultra-clean environment, we will need to recruit 22 630 patients in each group, that is, approximately 45 000 patients to attain a power of 80% with a significance level of 0.05. This will be our target population. We expect a very low drop-out rate/missing data in the study, estimated to be <1%. At the interim analysis, the p value will be set 10 times lower at 0.005, that is, if a statistically significant result between the groups is observed at 18 months, the study will be stopped. See figure 3 and online supplemental appendix 1 for details in R and explanation of the script for the sample size analysis.

10.1136/bmjopen-2020-047500.supp1Supplementary data

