## Methods: an assignment of interventions

### Allocation

The three PAP devices in each OR will synchronically be randomised in periods of 4 weeks, 6 weeks or 8 weeks to either have the system ‘on’ or ‘off’. The switch will always occur midnight Friday in order to limit the patients exposed to partial effect during the first 2 days after switching status. The system can be programmed to be active (ie, plasma chamber eradicating bacteria) at any given timeframe. The manufacturer of the PAP devices will prepare the randomisation allocation and automatic execution of it. The randomisation sequence is at minimum 8 years long and will be submitted to a third, independent party, responsible for keeping the allocation secret until interim analyses or study end. At the interim analyses, only allocations up to that date will be released.

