### Blinding

The on/off only refers to the plasma chamber responsible for the antimicrobial effect. As the machine retains the air flow it will be impossible for staff, surgeons and patients to determine the status of the machine from the outside. The device will also automatically switch status, where the true status is concealed for all study participants, including other hospital personnel until the end of the study.

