### Data management

The study data will be securely managed and stored encrypted at a computer within Karolinska Institutet at Danderyd Hospital. No other than the authors stated above will gain access to raw data.

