### Statistical methods

The primary outcome is a binary variable where there are three groups. We will use logistic regression where the reference group is the placebo group, and the significance is related to the intervention group. The estimate for the mixed group is only for relating dose effect, that is, the group will not be pooled with either the placebo or the intervention group. Due to the randomisation, we do not intend to have any other covariates as confounders in the model. Similar methodology will be applied to the antibiotic’s binary outcome. The number of days with antibiotics will be modelled using a linear regression with the similar interpretation to above regarding predictors. Mortality will be modelled using a Cox proportional hazards model with time since surgery calculated as time to death, migration or 2 years. The Cox model will not contain any covariates due to the randomised study nature. The analysis will be performed by an epidemiologist/statistician in our team (MG) and will be performed as a per-protocol analysis.

We will handle confounding by including only the patient’s first surgical procedure. The randomisation process will handle other confounding such as confounding by selection. Procedural confounding will be handled by the external part who has done the randomisation procedure for each PAP device. Regarding dropouts, the healthcare registers and chart review done in the study will ensure a very low (<1%) drop-out rate. Individual patients can also request that they are excluded from the registers and thus from the study, but by experience, this is very rare and will also not affect our ability to analyse our primary and secondary endpoints.

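### Between-group interim results go to the trial's own researchers and allocations to date are released, contrary to the promise of concealment until study end; the chart review of interim patients is the exposed step

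*Protocol article*

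**What the plan says.** All places are in the protocol article.

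- **Who sees interim results.** Ethics and dissemination: "The interim analysis results from the study will be presented only to the researchers involved unless the study thereafter is interrupted". The Abstract says the same.
- **What those results are.** Multicentre power with ultra-clean air sets an interim significance level of 0.005 and adds that "if a statistically significant result between the groups is observed at 18 months, the study will be stopped". The researchers are therefore shown a comparison of the groups, not only recruitment counts.
- **What happens to the allocation.** Allocation gives the sequence to an independent party "responsible for keeping the allocation secret until interim analyses or study end", and adds: "At the interim analyses, only allocations up to that date will be released". The recipient is not named.
- **What is promised.** Blinding states that "the true status is concealed for all study participants, including other hospital personnel until the end of the study".
- **Who handles the data.** Statistical methods: "The analysis will be performed by an epidemiologist/statistician in our team". Data management: "No other than the authors stated above will gain access to raw data".
- **What outcome work follows.** Outcomes describes a second step in which the charts of all trigger-positive patients are reviewed against the CDC definition before an infection is finally established.

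**The concern.** The article presents the double blind as a main strength of the trial. Concealment until the end of the study cannot be squared with a release of every operating room's on/off history at an interim 12 or 18 months into an inclusion period of nearly five years. Operating room and date of surgery are among the data fields collected, so anyone who holds the released sequence can read off a patient's group.

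Two things are at stake. First, the CDC criteria in Box 1 leave room for judgement, for example on whether a deep infection appears related to the operation. A reviewer who knows the group, or the trend, may judge charts differently by group. Second, people who know the trend go on to take decisions on conduct and analysis that the article leaves partly open:

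- Recruitment ends at a minimum of 45 000, not at a fixed number.
- Local or national register data are used as available.
- The per-protocol analysis depends on device status, which is validated retrospectively at the end of inclusion.

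**Working it through.** **1. The passages side by side.** The Allocation section ends secrecy at the interim for all operating-room dates so far. The Blinding section ends it at study end. Recruitment continues after the interim unless the trial is stopped, so the two dates differ. That results by group reach the researchers is explicit. That the allocations reach the team is an inference: the analyst belongs to the team and only the authors may hold raw data.

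**2. The plan's own figure.** Inputs from the Sample size section: infection rate 2%, reduction 25% (2.0% to 1.5%), and unrelated infections below 2% (2% used), added to both groups. This gives 4.0% v 3.5%. With two-sided 0.05 and 80% power:

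n = [1.960·√(2 × 0.0375 × 0.9625) + 0.8416·√(0.04 × 0.96 + 0.035 × 0.965)]² / 0.005² = 22 663 per group.

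The article states 22 630, a difference of 0.15%. The present point does not alter the sample size. The check only supports 3.75% as the average trigger rate implied by the plan.

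**3. Share of patients at the interim.** Inclusion from mid-April 2017 to 31 December 2021 is about 56.5 months. Even accrual is an assumption.

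| | 12 months (Data monitoring) | 18 months (power section) |
|---|---|---|
| Patients, 45 000 × m/56.5 | 9 558 | 14 336 |
| Share of 45 000 | 21% | 32% |
| Trigger-positive charts, × 0.0375 | about 358 | about 538 |
| Still inside the 12-week window | 12/52.18 = 23% | 12/78.27 = 15% |

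On either date about 2 200 patients (0.23 × 9 558 or 0.153 × 14 336) have an open primary-outcome window, so chart review for the interim cohort cannot be closed when allocations are released. No patient has reached the 2-year mortality endpoint either, but knowledge of allocation is unlikely to bias death.

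**4. Illustration of size.** Assume, without any source in the article, equal triggers in both groups, with 55% confirmed in one group and 50% in the other in every interim chart, and equal confirmation elsewhere.

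- Within the interim share: 0.55/0.50 = 1.10.
- Whole trial, interim at 12 months: 0.212 × 1.10 + 0.788 × 1.00 = 1.021.
- Whole trial, interim at 18 months: 0.319 × 1.10 + 0.681 × 1.00 = 1.032.

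The shift is about 2-3% and could go in either direction. If every chart with a closed window had been reviewed before the release, the exposed share would fall to about 2 200/45 000 = 4.9%, and the shift to about 0.5%.

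**The case against.** The strongest reply is that little of the blind is actually lost. Interim patients were operated on under concealed status, later allocations are withheld, and the Blinding section keeps surgeons, staff and patients unaware. The triggers are register codes, published in advance, which knowledge of the allocation cannot move. One CDC criterion is a diagnosis by a surgeon or attending physician, on its face that of a blinded treating clinician. The allocations may go to a single analyst. Masking of chart reviewers and an interim charter may sit in documents not shown, and the date of chart review is not given.

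Most of this stands. A reader might infer that the double blind ends for the interim patients, or that the investigators are documented as receiving the allocation list. The article supports neither. A reader might also set a 10% shift against the 25% effect sought. That compares a shift within 21-32% of patients with a whole-trial effect, and it rests on an assumed confirmation split. Nor is the absence of a masking rule in a journal article a fault in itself.

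The stated rules remain. Results by group go to the researchers, and the release of allocations contradicts the concealment statement. Fuller documents could clarify these rules, but the article as written does not merely leave them out.

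**Conclusion.** The point holds in a limited form. The article gives the researchers a between-group interim result and releases allocations to date, in conflict with its own statement on concealment. The exposed parts are the judgement-based chart review of up to 21-32% of patients and later decisions by people who know the trend. The plausible effect on chart-confirmed infection is modest: about 2-3% on the whole-trial relative risk under an illustrative assumption applied to all interim charts, and less if many were reviewed before the release. The register-trigger composite is unaffected by this route.

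The conclusion assumes even accrual and, for the allocations only, that the trial team is the recipient. The disclosure of results needs no such assumption. This should be corrected, but it does not by itself undermine the trial.

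**What to change.** Reconcile the Allocation, Blinding, and Ethics and dissemination sections as follows.

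1. The independent party that holds the sequence, or a statistician outside the team, runs the prespecified interim test and returns only *stop* or *continue*.
2. No allocation or result by group reaches investigators or chart reviewers until adjudication is complete and the database is locked.
3. Where allocations have already been released, the remaining charts are reviewed with operating room and date of surgery masked, and the report says so.

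Data management and Statistical methods need a matching exception so that an outside analyst may use the data. The cost is a short interim charter and a masked review form. The independent party already exists. The one real downside is that the team does not see the trend.
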